## Abstract

**Background:**

Chronic subdural hematoma (cSDH) is a common neurosurgical disease. It is often considered to be a rather benign entity. In spite of well established surgical procedures cSDH is complicated by a recurrence rate up to 30%. Since glucocorticoids have been used for treatment of cSDH in 1962 their role is still discussed controversially in lack of evident data. On the basis of the ascertained inflammation cycle in cSDH dexamethasone will be an ideal substance for a short lasting, concomitant treatment protocol.

Objective: to test the efficacy of dexamethasone on reduction inthe reoperation rate of cSDH.

**Methods/Design:**

The study is designed as a double-blind randomized placebo-controlled trial 820 patients who are operated for cSDH and from the age of 25 years are included after obtaining informed consent. They are randomized for administration of dexamethasone (16-16-12-12-8-4 mg/d) or placebo (maltodextrin) during the first 48 hours after surgery. The type I error is 5% and the type II error is 20%. The primary endpoint is the reoperation within 12 weeks postoperative.

**Discussion:**

This study tests whether dexamethasone administered over 6 days is a safe and potent agent in relapse prevention for evacuated cSDH.

**Trial registration:**

EudraCT 201100354442

## Background

Chronic subdural hematoma (cSDH) is a common neurosurgical disease: Its one-year incidence rate is about 5 per 100,000 in the general population, but increases for those aged 70 years and older (58 per 100,000 per year)
[1]. Because the proportion of people aged 65 years and older is expected to double worldwide between 2000 and 2030
[2], a large rise in incidence is expected.

Despite its relatively high mortality and morbidity it is often considered to be a rather benign entity
[3,4]. The main risk defining the outcome is recurrence. Even if operated by skillful neurosurgeons, recurrence rates from 3.8 to 30% are reported
[4-6].

cSDH was first described by JJ Wepfer
[7] in 1656, followed by Rudolf Virchow,
[8] who detected an inflammatory element and in 1856 named this condition *pachymeningitis haemorrhagica interna*. The formation of new membranes and the extravasation of fluid in the cavity between these membranes and layers was seen by Virchow as typical for this disease. Today’s definition of chronic subdural hematoma as a 'chronic, self-perpetuating inflammatory process that involves the dura mater' was given by Frati
[9] and confirms the inflammatory nature of this disease.

Several causes have been described as mechanisms of origin. Analogous to acute subdural hematoma caused by trauma, the occurrence of chronic subdural hematoma has often been described in conjunction with head injury. Histopathological evidence for the influence of trauma was given by Schachenmayr
[10] in 1978 describing that after microtrauma a cleavage of the inner dural layer occurs ('tissue torn artifact'). Still today the role of head trauma in the origin of chronic subdural hematoma is not clear. A literature search discloses that at least mild head trauma had occurred in 8%
[11] to 80%
[12] of the patients.

An important histopathological mechanism of origin is the high non-specific reaction potential of the capillary network in the inner dural sheet which, coming in contact with blood or fibrin degredation products, leads to the formation of a neomembrane. This mechanism is supported by the inflow of liquids like blood, later plasma and/or cerebrospinal fluid (CSF. Further progression is maintained by tissue activator (TA) exuding from the extremely vascularized membranes into the cavity, perpetuating a fibrin/fibrinogene mechanism leading to continuous microhemorrhages. Furthermore the automembrane developes inflammatory cells, like mastcells, eosinophiles, neutrophiles, monocyts, macrophages, endothelial cells and fibroblasts, being continuously activated and recruited. This constitutes a source of inflammatory angiogenic fibrinolytic and coagulation factors
[9].

The symptomatology consists of headache, neurological focal symptoms, aphasia, epilepsy and unconsciousness. After assessment of the symptoms a neurological classification can be made grading the patients from grade 0 to grade 4
[12]. The main diagnosis however, is done by imaging. Computerized tomography (CT) and magnetic resonance imaging (MRI) disclose monolateral or bilateral extracerebral fluid with more or less membranes separating the hematoma into chambers. Different classifications for both imaging tools are available
[13-15].

The primary therapeutic option is surgery. The standard procedure consists of a burr hole above the site of the lesion with or without irrigation. Santarius
[16] has proved that an insertion of a drain diminishes recurrence and mortality at 6 months after burr hole craniostomy. In cases of separation of the hematoma by thick layers, open craniotomy must be chosen to allow for evacuation of all chambers
[17]. Recurrence of the hematoma is defined as reappearance of the clinical and radiological symptoms and leads to reoperation.

The first remark about a nonsurgical treatment of cSDH was given by Ambrosetto
[18] in 1962. He described four patients, who received a conservative multimodal therapy in combination with corticosteroids: Their clinical symptoms regressed completely. Frati
[9] and Labadie
[19,20] reported that due to the proof of proinflammatory and inflammatory cytogene that anti-inflammatory therapy may be beneficial. However, several national surveys show a controversial use of cortisone in treatment of cSDH: 38% of French neurosurgeons use adjuvant corticosteroid therapy after surgery
[21]. For 13% of Canadian neurosurgeons cortisone plays a role in the treatment of cSDH
[22], and 55% of surgeons in the UK and Ireland prescribe steroids in conservatively managed patients
[23]. Berghauser Pont
[24] wrote about a generous use of corticosteroids in a nonsurgical setting and in preparation for surgery respectively, in combination with surgical treatment in the Netherlands.

There are only poor data published about the efficacy of concomitant cortisone medication. Sun
[25] describes 112 cases treated in a prospective set-up. A systematic review regarding corticosteroids and cSDH
[26] found that beyond Sun’s trial there are only four retrospective studies and concludes that steroids are beneficial and suggests more prospective data are needed. Berghauser Pont also performed a retrospective cohort study
[27] of patients with cSDH on preoperative corticosteroid therapy. If there were no signs of recovery patients underwent surgery: 496 patients with burr hole craniostomy were enrolled. Recurrence was stated at 11.9. In spite of preselection the basis of cortisone therapy, the relapse rate is low.

In 2011 Park published a prospective study about cSDH
[28]: 31 patients underwent burr hole irrigation plus external drainage. The objective of this study was to investigate the relationship between fibrinolytic factors and computed tomography findings. We emphasize in this trial the postoperative administration of dexamethasone for one week, because the reoperation rate Park described was only 3.2.

Thus, the DRESH study will be the first randomized controlled trial (RCT) to evaluate the role of a short postoperative cortisone protocol in the operative treatment of cSDH.

### Choice of comparator

Dexamethasone has been selected because contrary to methylprednisolone, it is independent of weight, allowing for a simplified randomization and blinding procedure. Other advantages of dexamethasone are the longest biological half-life of all glucocorticoids (36 to 54 hours) and seven times higher potency than prednisolone. The total dosage used in the DRESH study is 68 mg in Austria and 68.25 mg in China, which is equivalent to a two times higher dosage of prednisolone (1 mg/kg/day). The drug concentration in CSF correlates with the peak concentration in plasma. The DRESH study considers these pharmacokinetics by a single dose at a physiological time in the morning.

### Study objectives

#### Primary objective

The primary objective is to demonstrate that dexamethasone reduces the reoperation rate by 50% within 12 weeks after hematoma evacuation.

#### Secondary objectives

The secondary objectives of the study are as follows: to measure the effect of dexamethasone on clinical outcome by the Markwalder score during a period of 12 weeks after surgery; the impact on radiologic signs of the hematoma, such as thickness, membranes and mass-demanding effect (midline-shift); to evaluate risk factors of the genesis and recurrence of cSDH in a prospective study design; risk of infectious complications, for example, pneumonia, urinary tract infection, ventriculitis, meningitis and encephalitis; dexamethasone-dependent severe psychiatric reactions; and death.

### Trial design

This is a phase III, prospective, multi-center, double blind, randomized, placebo-controlled study. Eligible participants are randomized in a 1:1 allocation ratio to one of the two arms: an intervention arm, in which the participants receive dexamethasone according to the protocol, and a control arm in which they receive placebo.

### Inclusion criteria

The inclusion criteria are: 1) patients who are to undergo surgery for cSDH according to one or both of the following criteria: clinical symptomatology (Markwalder grade 1 to 4) with correlation to the cerebral lesion, or radiologic finding of cSDH with flattening of the underlying cortex and/or midline shift more than 5 mm; and 2) male or female patients aged over 25 years (inclusive).

### Exclusion criteria

The exclusion criteria are: 1) pregnancy and nursing; 2) diabetes; 3) hypertension (systolic blood pressure (SBP) >180 mmHg) that is refractory to treatment; 4) glaucoma; 5) Known hypersensitivity to dexamethasone; 6) known peptic ulceration; 7) acute systemic infection (fever, leucocytosis, elevated C-reactive protein (CRP) and/or PCT (Procalcitonin); 8) parasitic infection; 9) current or previous history of severe affective disorders (especially previous steroid psychosis); 10) recent myocardial infarction (as myocardial rupture has been reported); 11) patients for whom study drug cannot be started within 48 hours after evacuation of the hematoma; 12) patients for whom it is known at the time of screening that certain follow-up, protocol-mandated imaging assessments will not be feasible; 13) patients unlikely to comply with the protocol (for example, unable to return for follow-up visits); 14) current alcohol or drug abuse, or dependence; 15) use of another investigational product within 28 days prior to randomization; 16) vitamin-K antagonists during the first 2 weeks after operation; 17) GpIIb/IIIa-receptor antagonists, ASS (acetylsalicylic acid) or NOAC (new oral anticoagulants) during the first two weeks after surgery; and 18)reoperation within 48 hours after the first operation.

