#### Concomitant care

All patients in the study will receive the routine standard of care. This will include a check of blood and vital parameters, a neurologic investigation and CT scan at admission. An acute onset of neurologic deterioration or a decline of alertness will need an urgent operative treatment. For neurosurgical procedures normal coagulation parameters are essential. In warfarin medication, the international normalized ratio (INR) has to be normal prior to surgery. Coagulation factors or other blood products will be administered as required. ASS is to be stopped five days and GpIIb/IIIa-receptor antagonists seven days before surgery, and NOAC a duration longer than double of their pharmacological half-life. Only those patients are eligible who are able either to pause their anticoagulant or antiplatelet medication, or to tolerate a conversion to LMWH (low molecular weight heparin) for two weeks postoperatively.

In consideration of different techniques available for the evacuation of a chronic subdural hematoma, the following procedure has been agreed: one burr hole over the site of the hematoma, no irrigation and a closed drainage system. The drain will be continued up to 48 hours. Criteria for discontinuing before 48 hours are air in the system, an incorrigible flow arrest or delivery of pure CSF.

Pain will be treated according to the WHO guidelines
[29].

LWMH are used for deep venous thrombosis prophylaxis. The application has to start within 24 hours postoperatively, or if the patient is mobile, less than 3 hours a day. Daily neurologic investigations and control of vital parameters and wound healing will be added to standard care, as will concerted medication and drawing of blood samples, CT scans and physical therapy as necessary.

There will be a focus on hyponatremia and pathologic INR values. Patients who received oral anticoagulation preoperatively will need to be controlled daily and will have to have their parameters kept within the normal range throughout the hospital stay. The same procedure will be applied in hyponatremia. At study day-3 blood glucose levels are evaluated. At a level higher than 300 mg/dl the patient will be excluded from the trial. In order to detect a raised intraocular pressure a measurement will be performed during the treatment period.

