### Data analysis

The primary endpoint is the rate of reoperation between 48 hours and 12 weeks after the initial evacuation of a chronic subdural hematoma. Mandatory reoperation during the first 48 hours is related to surgical complications. In such rare cases the patient will be excluded.

Evaluation of the Markwalder score will be done by computing crosstabulation tables and applying Pearson’s chi-square test. Data will be checked carefully for outliers and for normality based on the Kolmogrov-Smirnov test and Liliefors test. To evaluate the impact of dexamethasone on the thickness of the hematoma and other continuously distributed, metrically scaled variables, mixed models with treatment group as the independent factor and time as the repeated factor will be applied (if all assumptions for the model are met). Linearity will be assessed by Box Tidwell and log transformation. Corresponding planned contrasts together with 95% confidence intervals will be computed. If these variables do not fulfill the assumptions for parametric testing, nonparametric methods such as the bootstrap *t*-test, Kruskal-Wallis analysis of variance (ANOVA) with median tests and Friedman ANOVA with Wilcoxon matched-pairs test will be applied: 95% confidence intervals based on Pearson-Clopper values will be computed to estimate the reoperation rate in both groups. An unconditional test (Barnard’s test for superiority) for the ratio of these two proportions will be used. A *P*-value less than 5% will be considered statistically significant. All analyses will be done by one of the authors (WH) using STATISTICA 10 (Hill, T and Lewicki, P (2011). *STATISTICS: Methods and Applications*. StatSoft, Tulsa, OK, USA), StatXact 6.0 (Cytel Software Corporation (2003) Cytel Software Corporation, Cambridge MA, USA), NCSS 8 and PASS 11 Hintze, J (2012), NCSS 8, NCSS, LLC, Kaysville, UT, USA. (http://www.ncss.com).

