### Methodology

The DRESH study has a straightforward design: on the one hand an efficient concomitant treatment which should be evaluated to the highest evidence possible, and on the other hand the study dependent measures are perfectly integrated into the clinical routine. In the light of this aspect three points are worth mentioning: a clear study design and statistics, waived SAEs and a maximal time frame for randomization. Even patients who undergo emergency surgery can be randomized postoperatively. Most of the exclusion criteria are due to the use of dexamethasone or anticoagulant drugs. There is a simple primary endpoint defined without any surrogate parameter: reoperation. The reoperation rate should be decreased by 50%, because only 82 patients out of 820 (assumed reoperation rate of 10%) are affected and might benefit from the cortisone regime. In the case of a reduction in reoperation less than 50% more than 95% of the study population would take dexamethasone in vain. The surgical procedure has been standardized in order to achieve meaningful statistics.

The national authorities concerned have allowed waiving of particular SAEs, because dexamethasone has been used for decades. Hence, there is a clear understanding of the difference between drug-related and disease-related AEs. Evaluation of secondary objectives will be very lucrative because of the huge sample size. It will offer a refined knowledge of risk factors, the role of co-medication and radiologic findings. Nevertheless, the DRESH study has to clear two hurdles: to be the first RCT to prove significant efficacy for cortisone in the treatment of cSDH in general, and to test a reasonable medication dosage as a relapse prevention for surgical patients in particular.

In the event of significant results a powerful adjuvant therapy in preventing patients from reoperation is offered. For multi-morbid patients with high risk for surgery, a stand-alone therapy with dexamethasone is conceivable.

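### Exclusion criteria 16 and 17 turn on drug use that falls mostly after randomisation, so they cannot be verified at entry and conflict with the eligibility rule under Concomitant care

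*Protocol article*

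**What the plan says.** Two sections of the protocol article govern the same drugs over the same period.

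- **Exclusion criteria.** Criterion 16 lists "vitamin-K antagonists during the first 2 weeks after operation". Criterion 17 lists GpIIb/IIIa-receptor antagonists, "ASS (acetylsalicylic acid) or NOAC (new oral anticoagulants) during the first two weeks after surgery". Both are worded as use, with no qualifier such as planned or foreseen.
- **Concomitant care.** The condition here is about capability: "Only those patients are eligible who are able either to pause their anticoagulant or antiplatelet medication", or to tolerate "conversion to LMWH (low molecular weight heparin) for two weeks postoperatively".

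The timing of randomisation follows from three places. Criterion 11 excludes "patients for whom study drug cannot be started within 48 hours after evacuation of the hematoma". Table 2 marks randomisation under Screening. The Methodology section adds: "Even patients who undergo emergency surgery can be randomized postoperatively".

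Two other rules exclude a patient on something that happens later. Concomitant care excludes a patient from the trial if blood glucose on study day 3 is above 300 mg/dl. For reoperation in the first 48 hours, which is also criterion 18, Data analysis says: "In such rare cases the patient will be excluded".

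**The concern.** An exclusion criterion should be decidable when the patient is randomised. Criteria 16 and 17 are not, because they ask what the patient takes over a fortnight that has barely begun, or has not begun, at that moment. A site following the list literally would find that a properly randomised patient meets an exclusion criterion days later, possibly after the six-day study-drug course has ended.

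What is at stake is the randomised comparison of reoperation rates. Whether a patient goes back on an antithrombotic within two weeks may depend on how recovery goes, and recovery may depend on treatment. If such patients were dropped, the two arms would be compared on subsets selected after randomisation. If some sites dropped them and others did not, the analysed population would also depend on how each site read the text.

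**Working it through.** The plan gives no figure on this point, so there is nothing to reproduce. Its power calculation does not depend on it.

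**Step 1: how much of the window is unknown at entry.**
- Window in criteria 16 and 17: day 0 to day 14 after surgery.
- Latest start of study drug, and so latest randomisation: 48 hours, that is day 2 (criterion 11).
- Window after randomisation: 14 − 2 = 12 days at least, or 12/14 = 86%. If randomisation takes place at screening before surgery, all 14 days are unknown.

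**Step 2: the two rules applied to the same patients.**

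| Patient | Concomitant care | Criteria 16 and 17 |
|---|---|---|
| Can neither pause nor convert | not eligible | excluded |
| Can pause, takes none for 14 days | eligible | not excluded |
| Can pause at entry, restarts on day 10 | eligible | meets an exclusion criterion |

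The rules part in the third row, and neither section is given precedence.

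**Step 3: does the list elsewhere use entry-time wording?** Yes. Criterion 12 is limited to what is known at screening, criterion 13 to the likelihood of complying, and criterion 15 to the 28 days before randomisation. Criteria 16 and 17 carry no such limit. Criterion 18, next in the list, is an event after surgery, and Data analysis does act on it by exclusion.

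**Step 4: would later use be seen?** Table 2, footnote 2, ends the recording of concomitant medication with study drug. A six-day course starting between day 0 and day 2 ends at about day 6 to day 8, so use from then to day 14 may go unrecorded. The Week 4 column of the same row is ticked, which points the other way.

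**Step 5: illustration of bias, on assumed inputs only.** The documents give no restart rate and no reoperation rate among restarters. Suppose restarters are reoperated at 30% and all others at 10%.
- 10% of verum and 5% of placebo patients restart. All randomised: verum 0.90 × 0.10 + 0.10 × 0.30 = 12%; placebo 0.95 × 0.10 + 0.05 × 0.30 = 11%. After removing restarters: 10% against 10%. A one-point disadvantage disappears.
- Restart rates swapped between arms. All randomised: verum 11%, placebo 12%. After removal: again 10% against 10%. A one-point benefit disappears.

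The example shows the mechanism, and that its direction depends on inputs the documents do not give. It is not an estimate.

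**The case against.** The strongest reply is that criteria 16 and 17 are shorthand for the rule in Concomitant care, which covers the same drugs and the same two weeks and is decidable at entry. Where the protocol wants later removal it says so, for glucose and for early reoperation, and it says nothing of the kind for antithrombotics. The recording limit in footnote 2 also fits a rule applied at entry. Much of this stands. The entry-time reading may well be the intended one. It does not remove the conflict, because the printed criteria say something else and the same protocol uses exclusion for later events.

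Three stronger readings are tempting and are not supported:

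- **That the criteria remove randomised patients.** No section orders withdrawal or omission from the analysis for later antithrombotic use. The text permits that reading but does not prescribe it.
- **That the routine early CT carries a treatment effect into restart decisions.** Table 2, footnote 6, places that scan within 48 hours of surgery, while study drug may start as late as 48 hours, so the scan comes before treatment or very early in it. The text puts the next routine scan at week 4, outside the window. The Table 2 header's 16±7 days (day 9 to day 23) disagrees, but that is a separate inconsistency. Clinical recovery and unscheduled scans remain as possible routes.
- **That the trial loses power.** No restart rate is given, and the increase from 370 to 410 per arm allows for 40/410 = 9.8% loss, which could absorb some removals.

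It may also be said that the handling of deviations belongs in the analysis plan or full protocol. That is right for the detail. But the eligibility criteria are printed here, and it is their wording that opens the question.

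**Conclusion.** The point holds as a contradiction between two sections. Criteria 16 and 17 rest on conduct of which at least 12 of 14 days lie after randomisation, and they give a different answer from Concomitant care for any patient who could pause and later restarts. If the criteria were applied literally, the primary comparison would be conditioned on a post-randomisation event. The resulting bias could go either way, and its size cannot be derived from the documents. The conclusion assumes only that randomisation is no later than the start of study drug. It does not claim that such removals are planned. The defect is modest, but it bears on the primary analysis population and should be corrected.

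**What to change.** Reconcile the two sections by wording criteria 16 and 17 as a condition that can be judged at randomisation, consistent with the rule in Concomitant care. Add one sentence: a patient who takes one of these drugs after randomisation stays in the trial's primary analysis in the arm assigned, and the use is recorded as a deviation. For that record to be complete, footnote 2 and the Week 4 tick in Table 2 need to agree on recording through the two-week window.

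This does not alter which antithrombotic management is required. The cost is the wording of two criteria, one analysis sentence and, if footnote 2 now governs, about a week more of medication recording. The statistical downside is slight dilution of the treatment contrast by exposed patients who remain in the analysis.
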